#### IRT

2.11.2.

An infrared thermography camera (NEC InfRec R450, Avio Infrared Technologies Co., Ltd., Tokyo) with measuring wavelengths of 8–14 um, a temperature resolution of 0.025°C, and a resolution of 640 × 480 pixels, will be used to record thermal images to assess the heat radiation properties of the acupuncture points. By adjusting the height and angle of the machine, the subject’s measured sites will be on the camera screen distinctly. One researcher will use a cotton swab to mark the tested acupoints, and another researcher will operate the electronic cursor of the camera to the corresponding acupoint localization and record the coordinates. Turn off the lights and focus on the camera, then start recording the thermal images. Using the interval shooting mode, 1 thermal image will be taken automatically every 10s, and 1 min continuously, a total of 6 thermal images will be taken. The subject will be instructed to remain still during the measurement.

The InfRec Analyzer NS9500 (Avio Infrared Technologies Co., Ltd., Tokyo) will analyze all thermal images, displaying different temperatures in different colors and selecting the region where the temperature will be measured. The temperature data collecting parameter of the region of interest (ROI) will be set up as a circular area within a radius of 5 mm from the acupoint, which will be the same size as an acupoint in this study. TROI will be used as the average temperature of the ROI in 1 thermal image. The average TROI in the 6 thermal images will be calculated as the temperature of the acupoint (T_acupoint_). The top 4 acupoints most associated with MDD in IRT test will be selected as TSA by logistic regression analysis.

**Figure 3 fig3:**
[figure not shown]
The appearance of intradermal needle.

#### WL group

2.12.1.

Patients in this group will not receive IA treatment during the study period. When the study is over, they will receive 6 weeks of the same IA treatment as in the CCA group.

#### CCA group

2.12.2.

LR3 (Taichong), PC6 (Neiguan), SP6 (Sanyinjiao) and HT7 (Shengmen) will be stimulated in this group. PC6 and HT7 will use φ0.20*1.2 mm needle, as well as LR3 and SP6 will use φ0.20*1.5 m needle. After routinely disinfecting the skin around the selected acupoints, press the needle to insert the acupoint vertically and retain it in the skin. After the intervention, the needle will be retained for 72 h with a day of rest after removal. Then the next treatment will be performed. During needle retention, participants will be instructed to press the acupoints 3–4 times a day for about 1 min each time, with the amount of stimulation as much as the patient can tolerate, at an interval of about 4 h. A total of 10 treatment sessions will be performed for 6 weeks.

#### PSA group

2.12.3.

PSA selected in Trial A will be stimulated. According to the location of the acupoint, φ0.20*1.5 m needles are selected for thick muscles and φ0.20*1.2 mm needles are selected for shallow muscles. The operation, and treatment sessions will be the same as the CCA group.

#### TSA group

2.12.4.

TSA selected in Trial A will be stimulated. The needle, operation, and treatment sessions will be the same as the PSA group.

### Outcome Measures

2.13.

#### Trial A

2.13.1.

(1) Pain sensitivity specificity: PPT of acupoints;

(2) Thermal specificity: temperature of acupoints.

#### Trial B

2.13.2.

(1) Primary outcome measures: change in the PHQ-9. The PHQ-9 scale is widely used in clinics to assess MDD symptoms and evaluate therapy response (28, 29). There are nine questions on the PHQ-9 scale, each with a score of 0–3 (none: 0; a few days: 1; more than half of the time: 2; almost every day: 3), for a total score of 0–27. PHQ-9 has been demonstrated to be reliable in studies because of its high sensitivity and specificity (30). The accuracy and ability of the PHQ-9 to detect depression results over time have been proven in studies, and it can be utilized as a valid prognostic indicator (31).

(2) Secondary outcome measures: (1) Change in the SF-36: the MOS 36-item Short Form health survey (SF-36) (32) consists of 36 items that provide a comprehensive assessment of the patient’s physical condition and emotional perception in 8 dimensions: physical function (PF), role physical (RP), body pain (BP), general health (GH), vitality (VT), social function (SF), role emotional (RE), and mental health (MH), (2) Pain sensitivity specificity: the PPT change of acupoints, (3) Thermal specificity: the T_acupoint_ change of acupoints.

The PHQ-9 and SF-36 will be assessed before intervention, at 3, 6 weeks after intervention and at the end of 4-week follow-up; biological specificities of acupoints will be assessed before intervention, at 6 weeks after treatment.

### Safety Assessment

2.14.

The safety assessment indicator is the frequency of adverse events (AEs) during treatment in the trial. AEs will be recorded, such as bleeding, hematoma, dizziness, pain at the needle site, and increased blood pressure caused by acupuncture. AEs related to drug administration mainly include drug allergy, gastrointestinal disorders, neurological symptoms such as headache or sleep abnormalities, etc. Whether or not the AEs are related to the treatment method of this study, they should be recorded in detail, including the date of occurrence, duration, severity, and treatment measures of the AEs, etc. Investigators will assess the relevance of AEs to treatment.

When AEs occur, patients will be documented and treated promptly and appropriately until they return to fully normal. For serious AEs, investigators should immediately report to the principal investigator and the ethics committee, who will decide whether the patients should be withdrawn.

### Quality Control

2.15.

Before the trial, all investigators will receive training on the study protocol and various standard operating procedures (SOP) according to their different roles, to improve internal observational consistency and interobserver consistency among investigators, ensure the reliability of clinical study findings, and reduce the risk of bias. All acupuncture operations will be performed by acupuncturists who are licensed physicians and have been independently practicing acupuncture for at least 3 years and require training in the clinical standard practice of this study. Western medicine prescriptions will be performed by experienced, uniformly trained specialists. All outcome assessors will participate in standard outcome assessment practice training and uniformly complete case report forms (CRFs). Throughout the trial, all study data will be collected on CRFs and entered into the electronic data capture (EDC) system by independent investigators promptly. In addition, to ensure data accuracy, each center will arrange for another independent investigator to verify the EDC system data against the CRF. Mid-trial withdrawals or drop-outs will be documented in detail.

Under the direction of the Data Safety Monitoring Committee, a data safety monitoring committee will be formed. This committee’s staff will be in charge of data monitoring and will have the authority to reveal blinded data. They will also verify the authenticity between the raw and recorded data. In addition, the investigators will strictly implement a monthly clinical study quality check and quarterly multi-center clinical study quality monitoring, and discuss difficulties and best solutions that arise throughout the trial to control inter-center bias.

All treatment expenses and outcome assessments will be provided free of charge to participants to encourage recruitment and compliance.

### Statistical Analysis

2.16.

Statistical analyses will be performed by a third-party statistician not involved in the pre-test using the statistical software SPSS 25.0 (SPSS Inc., Chicago, IL, United States). It will be expressed as counts and percentages for categorical variables. Continuous variables in normal distribution will be expressed as mean ± standard deviation, while skewed data will be expressed as median and interquartile range. The chi-Squared test will be used to compare group differences in dichotomous variables with baseline characteristics such as gender and age. Logistics regression analysis will be used to screen potentially superior acupoints. To analyze changes in continuous variables at multiple time intervals before and after the intervention, normally distributed data will be compared within and between groups using repeated measures analysis of variance (ANOVA). For within- or between-group comparisons, non-parametric test will be utilized for skewed distribution data. Statistical significance is defined as a *p* value <0.05.

The intention-to-treat approach will be adopted. Missing data (imputation of missing cases by regression and imputation from the last observation) and non-compliance will be subjected to sensitivity studies (analysis by protocol).

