### Randomization and allocation

2.9.

Trial A is a controlled observational trial without randomization and allocation.

Trial B will use a computerized central randomization system to randomize the participants in the dynamic stratified block, which is undertaken by Zhejiang Taimei Medical Technology Co. Each center will have an independent researcher log into the computerized central randomization system and generate a randomized sequence that divides eligible participants into 4 groups (WL group, CCA group, TSA group, and PSA group) in a 1:1:1:1 ratio. The researcher will have no contact with participants, acupuncturists, outcome assessors, and data statisticians. The allocation results will be stored in the central computerized randomization system password-protected.

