Although traditional acupuncture has some advantages in improving MDD, it still has some limitations, such as time-consuming and some people having a fear of acupuncture. IA is a special acupuncture therapy that provide soft continuous stimulation of targeted acupoints for several days. Comparing to traditional acupuncture, IA is safer, more convenient and painless. Previous studies have found no significant difference between shallow acupuncture, which is similar to IA to some extent, and conventional acupuncture in activation of the cerebral cortex associated with MDD (36, 37). Moreover, a preclinical study has shown that IA can improve the behavior of depressed mice, increase their serum 5-HT levels and effectively regulate the function of the hypothalamic pituitary adrenal axis (38). Therefore, in this study, IA will be used as an acupuncture intervention to observe the clinical efficacy of IA for MDD based on the altered biological specificity of acupoints.

Guideline for primary care of MDD (2021) recommends a medication trial period of 4–6 weeks for patients undergoing depression treatment (39). Acupuncture treatments for depressive disorders typically last 4 to 6 weeks, according to the most recent expert consensus of integrated traditional Chinese and Western medicine for depression disorder (40). There are many previous studies of acupuncture for MDD that also chose 6 weeks as the endpoint (41–43). As a result, we chose 6 weeks as the time point for evaluation of the final treatment. This supports the validity of our study and ensures that our findings are in line with current best practices in the treatment of MDD.

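### PHQ-9 should be analysed by one pre-specified baseline-adjusted model, not by repeated-measures ANOVA with baseline as a repeated level and a switch to rank tests for skewed data

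*Protocol article*

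**What the plan says.** The primary outcome of Trial B (section 2.13.2) is given as "Primary outcome measures: change in the PHQ-9", with no visit attached. The same section sets the schedule: "The PHQ-9 and SF-36 will be assessed before intervention, at 3, 6 weeks after intervention and at the end of 4-week follow-up". Table 1 places these visits at weeks 0, 3, 6 and 10. The Discussion gives the visit of main interest: "we chose 6 weeks as the time point for evaluation of the final treatment".

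Section 2.16 introduces the method with "To analyze changes in continuous variables at multiple time intervals before and after the intervention" and then states that "normally distributed data will be compared within and between groups using repeated measures analysis of variance (ANOVA". The next sentence sets the alternative: "For within- or between-group comparisons, non-parametric test will be utilized for skewed distribution data". The section names no covariate, no contrast, no rule for calling data skewed, and no particular non-parametric test.

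Section 2.9 says that a central system will "randomize the participants in the dynamic stratified block", without naming the strata. Section 2.5 sets 120 patients for Trial B and says that this was not based on a power calculation. With 1:1:1:1 allocation that is 30 per arm.

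**The concern.** The aim in section 2.1 is pairwise: are strong-response acupoints better than common ones? The stated analysis does not lead directly to that answer, for three reasons.

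- **Baseline is spent as an outcome.** Because the ANOVA covers values before and after the intervention, baseline PHQ-9 enters as a repeated level. Its use as a predictor of the week-6 score, which would sharpen the comparison, is given up.
- **The omnibus terms do not match the question.** The group main effect averages in a visit at which randomised arms have no expected difference. The group-by-time term tests all arms and all visits together.
- **The test depends on the data.** If PHQ-9 is judged skewed, a rank test replaces the ANOVA. The usual rank tests give no baseline-adjusted mean difference in PHQ-9, so the quantity reported changes with the shape of the data.

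With 30 patients per arm, and a sample size chosen without a power calculation, precision that is available from data already collected should not be given up.

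**Working it through.** The plan states no power or precision figure, so there is none to reproduce.

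**Inputs.** From the documents: 4 arms (2.1, 2.9), 4 PHQ-9 visits (2.13.2), and 120/4 = 30 patients per arm (2.5). Assumed, because the documents do not give it: the correlation rho between baseline and week-6 PHQ-9, taken as 0.3, 0.5 and 0.7. The variance ratio below needs no assumed SD or treatment effect.

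**Step 1: the omnibus terms.**
- The group main effect targets the average arm difference over four visits, with an expected 0 at baseline. If the effect is constant from week 3, this is (0+1+1+1)/4 = 75% of the week-6 effect. If half is present at week 3, it is (0+0.5+1+1)/4 = 62.5%.
- The group-by-time term has (4-1) x (4-1) = 9 degrees of freedom. A significant result does not say which arm is better or when.

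**Step 2: the most favourable reading, a week-6-minus-baseline contrast.** Take variance 1 at both visits. Per patient:
- change from baseline: 1 + 1 - 2 rho = 2(1-rho);
- week 6 adjusted for baseline: 1 - rho^2;
- ratio: 2(1-rho)/[(1-rho)(1+rho)] = 2/(1+rho).

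| rho | change | adjusted | ratio | 30 adjusted per arm is worth, unadjusted | 30 unadjusted per arm is worth, adjusted |
|---|---|---|---|---|---|
| 0.3 | 1.40 | 0.91 | 1.54 | 46.2 | 19.5 |
| 0.5 | 1.00 | 0.75 | 1.33 | 40.0 | 22.5 |
| 0.7 | 0.60 | 0.51 | 1.18 | 35.3 | 25.5 |

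The last two columns are 30 x ratio and 30 / ratio.

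**Step 3: cost of estimating the slope.** With one slope pooled over four arms there are 120 - 4 = 116 within-arm degrees of freedom. For a normally distributed baseline, the adjusted variance rises by a factor of about 1 + 1/(116-2) = 1.009, which is negligible.

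**Step 4: unequal variances.** Let s0 and s6 be the SDs at baseline and week 6. The change variance is s0^2 + s6^2 - 2 rho s0 s6 = (1-rho^2) s6^2 + (s0 - rho s6)^2. Apart from the small cost in step 3, it is never below the adjusted variance, and the two are equal only when s0 = rho s6. The direction therefore holds in general, but the size does not. With s0 = 0.8 s6 and rho = 0.5, the change variance is 0.64 + 1 - 0.80 = 0.84 against 0.75, a ratio of 1.12. Section 2.6 uses PHQ-9 for initial screening, so a narrower baseline spread is possible.

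**Step 5: the switch.** Sections 2.13.2 and 2.16 together allow a mean-based analysis if PHQ-9 looks normal and a rank-based one if it does not. These estimate different quantities, and the choice would be made after seeing the data.

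**The case against.** The strongest reply has four parts.

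- **The ANOVA can give the week-6 effect.** A reader might infer that the plan cannot estimate that effect, or that efficacy will be judged on the all-visit group term. The documents support neither. Section 2.16 speaks of analysing changes, which points to the group-by-time comparison, and a week-6-minus-baseline contrast by arm can be extracted. The diluted main effect is never named as the efficacy test, so the 75% and 62.5% show why that term should not be read; they are not the plan's chosen estimate.
- **Silence is not exclusion.** A reader might also infer that centre and strata are deliberately left out. Section 2.9 does not name the strata and section 2.16 says nothing about them. A full protocol or analysis plan, not shown here, may cover this, and the gain from adjusting cannot be computed.
- **It is a matter of efficiency.** A change-score contrast is unbiased in a randomised trial. This stands: the loss is precision, not validity. The Discussion also concedes a small sample and presents the results as basic data for later trials.
- **Power depends on unstated inputs.** Any scenario power would need an SD, an effect and a pattern across arms that the documents do not give, and it would set omnibus tests against a single contrast. No power loss is claimed here.

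That an article condenses the full plan does not dispose of the point. The article states the method, ANOVA on values before and after, and states the switch. A baseline-adjusted model with no switch would be a different plan from the one published.

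**Conclusion.** The point holds as one of efficiency and pre-specification. On the natural reading, section 2.16 uses baseline PHQ-9 as a repeated level instead of a covariate. Even the best contrast available from that analysis then has 2/(1+rho) times the variance of a baseline-adjusted comparison, or 18% to 54% more for rho from 0.7 down to 0.3. This rests on equal variances at baseline and week 6 and on assumed correlations. A smaller baseline spread can shrink the gain, but apart from the negligible cost of estimating the slope it does not reverse it.

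Separately, the move to an unnamed rank test for skewed data is stated in the text and makes the estimated quantity data-dependent. Whether PHQ-9 will in fact be skewed cannot be known from the documents. The change should be made, but the trial is not invalid without it.

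**What to change.** In section 2.16, replace the ANOVA and the switch, for PHQ-9, with one model fixed in advance whatever the distribution. Either of these would do:

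- ANCOVA of week-6 PHQ-9 on arm and baseline PHQ-9; or
- a mixed model over weeks 3, 6 and 10 with arm, visit, arm-by-visit and baseline PHQ-9.

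Include the stratification factors actually used in randomisation. Report the PSA-CCA and TSA-CCA differences at week 6 with confidence intervals, and name week 6 in section 2.13.2 so that it agrees with the Discussion. Deal with skewness through robust or bootstrap standard errors, or a rank-based sensitivity analysis, and not by changing the primary test.

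The cost is analysis wording only. Baseline PHQ-9 is already collected, no visit or patient is added, and the software named in section 2.16 can fit either model.

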**Methods:**

The first part of the study will enroll 30 MDD patients and 30 healthy control (HC) participants to assess pain sensitivity and thermal specificity of MDD-related acupoints using a pressure pain threshold gauge (PTG) and infrared thermography (IRT). The potentially superior acupoints for treating MDD will be selected based on the results of PTG and IRT tests and referred to as pressure pain threshold strong response acupoints (PSA) and temperature strong response acupoints (TSA).

The second part of the study will enroll 120 eligible MDD patients randomly assigned to waiting list (WL) group, clinical common acupoint (CCA) group, TSA group, and PSA group in a 1:1:1:1 ratio. The change in the Patient Health Questionnaire-9 Items (PHQ-9), the MOS item short-form health survey (SF-36), pressure pain threshold, temperature of acupoints, and adverse effects will be observed. The outcomes of PHQ-9 and SF-36 measures will be assessed before intervention, at 3 and 6 weeks after intervention, and at a 4-week follow-up. The biological specificity of acupoint measures will be assessed before intervention and at 6 weeks after intervention. All adverse effects will be assessed.

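### The only missing-data methods named for PHQ-9, last observation carried forward and regression imputation, are weak checks on an intention-to-treat result from repeated measures ANOVA

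*Protocol article*

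**What the plan says.** All references are to the protocol article.

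- **Outcome and visits (2.13.2).** "Primary outcome measures: change in the PHQ-9". The schedule is: "The PHQ-9 and SF-36 will be assessed before intervention, at 3, 6 weeks after intervention and at the end of 4-week follow-up". The Discussion makes week 6 the main time point: "we chose 6 weeks as the time point for evaluation of the final treatment".
- **Size (Abstract, Methods).** "The second part of the study will enroll 120 eligible MDD patients randomly assigned to waiting list (WL) group" and three other arms at 1:1:1:1, so 30 per arm. Section 2.5 says that this number does not come from a power calculation. No standard deviation, effect size or dropout rate is given.
- **Analysis (2.16).** "The intention-to-treat approach will be adopted". For the outcomes measured over time, "normally distributed data will be compared within and between groups using repeated measures analysis of variance (ANOVA").
- **Missing data (2.16).** One sentence names "imputation of missing cases by regression and imputation from the last observation", and the same sentence ends "non-compliance will be subjected to sensitivity studies (analysis by protocol"). It does not say whether the regression imputation is single or multiple, nor which method, if any, feeds the main ITT analysis.
- **Which data count (2.7 and 2.8).** Terminated patients enter the efficacy statistics only if they passed half of the treatment course. Patients whose incomplete data affect the assessment are eliminated.

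**The concern.** Every arm, including the waiting list, receives basic treatment with antidepressants (2.12), so PHQ-9 should fall everywhere. Under LOCF, a patient who leaves early is scored as if improvement had stopped. If one arm loses more patients, that error does not cancel. Unequal loss is plausible here, because waiting-list patients get no intradermal acupuncture during the study, while the other arms wear needles for 72 hours at a time over 10 sessions.

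Regression imputation has a different weakness. If each missing score is filled in once with its predicted value and then treated as observed, the residual spread is too small and p values are too small.

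The main model adds to the problem. Classical repeated measures ANOVA needs every visit, so without imputation it becomes a complete-case analysis under an ITT label. The checks meant to show whether missing data matter could then mislead, one through its estimate and the other through its precision.

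**Working it through.** **No figure to reproduce.** The article gives no power, standard deviation, effect or dropout rate. All sizes below rest on assumed inputs and are shown as ranges.

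**1. Listwise loss.** Assume that 5% or 10% of scores are missing at each of three post-baseline visits, independently.
- 30 × 0.95³ = 25.7 per arm
- 30 × 0.90³ = 21.9 per arm

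**2. LOCF bias by arithmetic, no true effect.** Assume that mean PHQ-9 falls 4 points by week 3 and 7 by week 6. Carrying baseline forward misstates week 6 by 7 points; carrying week 3 forward misstates it by 7 − 4 = 3. Spurious difference = (difference in dropout) × (error per dropout).
- 10% against 20%: 0.10 × 3 = 0.3 to 0.10 × 7 = 0.7 points
- 10% against 30%: 0.20 × 3 = 0.6 to 0.20 × 7 = 1.4 points

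**3. Simulation.** Two arms of 30, week-6 PHQ-9 analysed by baseline-adjusted ANCOVA, 4000 runs per scenario. Assumed: baseline mean 16, SD 5, correlation 0.6 between adjacent visits and 0.48 from baseline to week 6, and 60% of the decline reached by week 3. Dropout was random, half before week 3 and half after, unless stated. The Monte Carlo standard error of a 5% rejection rate is √(0.05 × 0.95 / 4000) = 0.34 percentage points. Full data rejected in 4.4% to 5.9% of null runs.

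LOCF (positive bias favours the active arm):

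| Decline WL / active | Dropout WL / active | Bias (points) | Null rejection |
|---|---|---|---|
| 6 / 6 | 10-30%, equal | about 0 | 4.4-5.5% |
| 6 / 6 | 30% / 10% | +0.88 | 11.1% |
| 6 / 6 | 40% / 10% | +1.24 | 17.3% |
| 6 / 6 | 30% / 10% nominal, dependent on week-3 score | +0.66 | 7.2% |
| 4 / 7 | 10% / 10% | −0.21 | – |
| 4 / 7 | 20% / 20% | −0.45 | – |
| 4 / 7 | 30% / 10% | +0.34 | – |
| 4 / 7 | 10% / 30% | −1.17 | – |

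A hand check agrees. With random dropout, half carry an error of the full decline d and half an error of 0.4d, so the mean error is 0.7d.
- 6 / 6, 30% / 10%: 0.20 × 0.7 × 6 = +0.84
- 4 / 7, 10% / 30%: 0.10 × 2.8 − 0.30 × 4.9 = −1.19

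The ratio of model to empirical standard error under LOCF was 0.97 to 1.03, so its precision was not overstated.

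Single deterministic regression imputation (from arm, baseline and week 3 where observed):

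| Dropout, both arms | Standard error ratio | Null rejection |
|---|---|---|
| 10% | 0.89-0.90 | 8.2% |
| 20% | 0.78-0.79 | 12.4% |
| 30% | 0.72 | 15.3% |

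Its bias stayed within 0.04 points of zero in every scenario, including those where dropout depended on the week-3 score. A second simulation (8000 runs per cell, imputing from baseline and arm only, t test on change, correlation 0.3 to 0.7) gave 6.6-7.7%, 9.8-10.7% and 12.9-15.3%.

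Complete cases under random dropout rejected in 4.9% to 5.7% of null runs. When dropout depended on the week-3 score at nominal 30% / 10%, they were biased by −0.22 points.

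**Not tested.** A mixed model and multiple imputation were not simulated, nor was the four-arm repeated measures ANOVA.

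**The case against.** The strongest reply is that both imputations stand in the sentence on sensitivity studies and that a condensed article may leave the main method, and the number of imputations, to a fuller document. This stands. A reader might infer that missing primary data are handled by LOCF and single regression imputation. The text does not say so: the main method is unstated, and the word single does not appear. The type I error figures for regression imputation therefore hold only if it is single.

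A reader might also conclude that both methods give biased estimates and intervals that are too narrow. The check does not bear that out. LOCF produced bias with sound standard errors; single regression produced small standard errors with almost no bias.

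A third tempting reading is that these analyses cannot support the ITT result at all. That is too strong. With balanced dropout and no true effect, LOCF was unbiased; with balanced dropout and a true 3-point effect, it moved modestly towards no effect. The article gives no dropout rate, and section 2.7 asks investigators to complete whatever assessments they can after termination, which should limit missing data.

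Finally, if the half-course rule in 2.7 governs, baseline would seldom be carried forward. Five of 10 sessions at 72 hours plus a rest day take 5 × 4 = 20 days, close to the week-3 visit. The lower LOCF figures (0.3 and 0.6) would then be nearer the mark. But that rule gets there by removing early terminators, which is itself at odds with ITT.

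What survives is that the article does choose two methods by name. The fault is in that choice and not in an omission.

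**Conclusion.** The point holds in a limited form and should be corrected before analysis. The two named imputations are weak checks on the primary PHQ-9 comparison, for separate reasons.

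- LOCF can create or hide a difference when dropout is unequal, in a direction that depends on which arm loses more patients. At 30% against 10% and no true effect, the bias of 0.88 points was about three quarters of the empirical standard error (0.88 / 1.20 = 0.73).
- Regression imputation, if single, can turn a nominal 5% test into one of about 8% to 15% at 10% to 30% missing.

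These sizes depend on the assumed decline, spread, correlation and dropout, none of which the article supplies. With low and balanced dropout the practical harm is small. The conflict between ITT and the efficacy-data rules in 2.7 and 2.8 does not depend on those assumptions, because the rules can take patients out before any missing-data method applies.

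**What to change.** In section 2.16:

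1. Make the primary analysis a likelihood-based mixed model for repeated measures, using all observed PHQ-9 visits of all randomised patients, with baseline PHQ-9 and centre in the model.
2. Drop LOCF.
3. State that any regression imputation is multiple imputation with pooled variance, from arm, baseline and earlier PHQ-9, and centre. Use sessions received only within the acupuncture arms, since the waiting list has none.
4. Add a delta-adjusted sensitivity analysis in which the shift for missing scores varies separately by arm. A common penalty on all acupuncture arms would test them against the waiting list but say little about PSA and TSA against CCA, which is the stated aim.
5. Reconcile the half-course rule in 2.7 and the elimination for incomplete data in 2.8 with ITT, so that it is clear which patients and data enter the primary analysis. This concerns the analysis set only, not when a patient should stop treatment.

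The cost is analysis wording and modest programming, with no added patients or visits. Intervals may be slightly wider; this was not computed.
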